#### Sample size calculation

Sample size determination was guided by a literature review and practical considerations, with 200 lung cancer patients and 100 healthy controls enrolled retrospectively for prediction model development. The sample size of the independent prospective cohort should consider recurrence prediction validation and 2-year DFS comparisons. On the basis of the calculations in Supplementary material 2, we plan to prospectively enroll 160 patients. Enrollment continuation will be determined by the investigator after the predefined sample size is met.

## Interventional substudy: MRD-based adaptive postoperative management for lung cancer

### Settings

This prospective multicenter real-world study aims to evaluate whether compared with standard management, ctDNA-MRD-guided postoperative surveillance and adjuvant therapy strategies improve clinical outcomes and cost-utility in patients with stage IA-IIIA NSCLC. We will prospectively enroll 756 patients across 10 clinical centers. Participants will undergo real-world preference allocation to either the standard treatment group or the ctDNA-MRD-guided treatment group, with longitudinal monitoring at 3–6-month intervals. The primary endpoint is the two-year DFS rate (Figure 2).

### Patient enrollment

Patients who have not been treated preoperatively or who have received neoadjuvant therapy will be recruited separately, with detailed inclusion/exclusion criteria provided in Table 3. During clinic visits or hospitalizations, researchers will confirm the eligibility of patients, obtain informed consent, and collect relevant study data and blood samples.

**Table 3 j_jtim-2026-0023_tab_003:** Inclusion and exclusion criteria for the interventional substudy

**Patients without neoadjuvant therapy (*n* = 609)**	
Inclusion	
	(a) Adults (≥18 years) with clinical stage IA-IIIA (8th edition) NSCLC that are scheduled for curative surgery;
	(b) Radiologically confirmed solid lesions with diameters ≥1 cm* or GGN with short-axis diameters ≥1.5 cm;
	(c) Signed informed consent.
Exclusion	
	(a) Pure GGN observed via chest CT;
	(b) History of any other malignancy within 5 years;
	(c) Has active infectious diseases;
	(d) Failure to undergo radical surgery;
	(e) Pathologically confirmed non-NSCLC;
	(f) Pathologically confirmed TNM stage IIIB-IV (8th edition);
	(g) Has received neoadjuvant therapy;
	(h) Life expectancy less than 12 weeks.
**Patients receiving neoadjuvant therapy (*n* = 147)**	
Inclusion	
	(a) Adults (≥18 years) with clinical TNM stage (8th edition) I-III NSCLC that are scheduled for neoadjuvant therapy;
	(b) Signed informed consent.
Exclusion	
	(a) History of any other malignancy within 5 years;
	(b) Has active infectious diseases;
	(c) Pathologically confirmed non-NSCLC;
	(d) Pathologically confirmed TNM stage IIIB-IV (8th edition) after neoadjuvant therapy;
	(e) Failure to obtain biopsy specimens before neoadjuvant therapy;
	(f) Failure to undergo radical surgery;
	(g) Life expectancy less than 12 weeks.

^*^Solid lesions with long-axis diameters measuring 1–1.5 cm also require short-axis diameters ≥1 cm to preserve adequate samples for baseline detection. NSCLC: non-small cell lung cancer; GGN: ground-glass nodule; CT: computed tomography.

### Data collection and testing

#### Data collection

Demographic characteristics, clinical profiles, and preoperative imaging findings will be obtained through electronic medical records review. Comprehensive documentation includes treatment details (surgical procedures, neoadjuvant therapy, and adjuvant therapy), therapeutic efficacy, and treatment-related adverse events. Pathological data from surgical specimens or biopsy samples, along with serial postoperative imaging examinations, ctDNA-MRD detection and prognostic outcomes during follow-up, will be prospectively recorded in a centralized research database.

**Figure 2 j_jtim-2026-0023_fig_002:**
[figure not shown]
Design of the interventional substudy. Participants will be stratified by preoperative treatment status (neoadjuvant therapy or upfront surgery). Allocation will follow real-world preferences to either the clinical standard management group (*n* = 378) or the ctDNA-MRD-guided treatment group (*n* = 378), with longitudinal monitoring at 3–6-month intervals. In the MRD-guided arm, postoperative management will be tailored according to serial MRD dynamics and integrated with pathological response assessments in neoadjuvant therapy subgroups. Two-year DFS will be evaluated as the primary outcome.

#### Collection and storage of biospecimens

The participants will have 24 mL of blood collected 0–3 days before the operation, 3–10 days after surgery, 1 month after surgery, and every 3–6 months during the three years of follow-up. We will allow a maximum deviation of ±1 month around each scheduled postoperative draw to accommodate clinical logistics. Sensitivity analyses will be performed by excluding samples collected outside the ±2-week window and re-estimating MRD dynamics and their correlation with outcomes to confirm the robustness of temporal patterns. Additional peripheral blood samples will be collected within 1 week before neoadjuvant therapy initiation and on Day 1 of each treatment cycle for patients receiving neoadjuvant regimens. For patients who require adjuvant therapy based on clinicopathological characteristics and MRD assessment, blood sampling will be conducted at the beginning of adjuvant therapy and immediately after the completion of adjuvant chemotherapy cycles, with subsequent sampling performed every 3–6 months. For patients deemed not to receive adjuvant therapy, regular blood monitoring will be performed at 3–6-month intervals.

Surgical specimens will be collected for tumor-informed ctDNA-MRD testing. The processing and preservation of the biospecimens are outlined in the observational substudy section.

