**Methods:**

We will recruit pathologically confirmed TNM stage IA-IIIA (8^th^ edition) NSCLC patients who are undergoing radical resection. Eligible participants will be divided into a standard treatment group and a ctDNA-guided group depending on their preference. Patients treated with or without neoadjuvant therapy will be studied in parallel. In the ctDNA-guided group, adjuvant therapy can be avoided for patients whose MRD is undetected at 1 month after surgery, and an additional requirement is to achieve a major pathological response for patients receiving neoadjuvant therapy. Imaging and MRD monitoring will be performed every 3–6 months for 3 years of follow-up, and postoperative management will be determined by the MRD results at each time point. Adjuvant therapy will be stopped if the patient's MRD status is continuously negative; otherwise, a treatment plan will be initiated after discussion among a multidisciplinary team (MDT). The recruitment phase began in April 2025, and 916 patients will be enrolled.

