### Interventions

#### Experimental arm (ctDNA-guided management)

In the ctDNA-guided arm, for treatment-naive patients, the results of ctDNA-MRD detected from blood before surgery, on Day 3 and 1 month after surgery will be provided to clinicians and patients 6–8 weeks after surgery. Notably, blood samples obtained on postoperative Day 3 may not be obtainable consistently in clinical practice. Thus, patients whose MRD is undetected 1 month after surgery will enter surveillance with blood sampling every 3–6 months during follow-up without additional adjuvant therapy. Blood samples obtained 3 days after surgery may serve as an alternative source of data in circumstances where blood sampling 1 month after surgery is not performed as planned. Furthermore, the concurrent availability of specimens from day 3 and 1 month after surgery facilitates a more robust assessment, wherein the Day 3 data provide supplementary context. Adjuvant therapy will be initiated if the patient’s MRD status is positive or if progression is suggested by imaging. The MDT will recommend specific treatment strategies on the basis of prior therapy, histology, and gene mutation. Treatment decisions will be individualized but guided by national guidelines to ensure consistency across centers.

For neoadjuvant-treated patients, ctDNA-MRD results of blood samples collected before/during neoadjuvant therapy, before surgery, and after surgery will be analyzed within 4–6 weeks after surgery. Patients will receive adjuvant therapy if any of the following criteria are met: the major pathological response is not reached (non-MPR) or postoperative ctDNA positivity conditions are met. Only patients who achieve MPR and negative ctDNA results 1 month after surgery will avoid adjuvant therapy, with surveillance of ctDNA-MRD detection performed every 3–6 months. Therapy will begin if ctDNA becomes positive.

If adjuvant therapy is indicated postoperatively after assessment, the MRD assessment will be performed after chemotherapy is completed (within weeks 3–4 in the final cycle of treatment).^[29]^ If MRD is positive, the patient will continue adjuvant therapy; otherwise, maintenance treatment will be stopped. Subsequent MRD monitoring should be performed every 3–6 months, with positive results or imaging progression triggering MDT discussion for treatment and negative results confirming therapy termination. If MRD persists after standard adjuvant cycles, the treatment duration will be extended.

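### The ±1 month sampling tolerance also covers the 1-month MRD draw that decides adjuvant therapy, so a compliant decision sample can fall anywhere from day 0 to about day 61

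*Protocol article*

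**What the plan says.** The sampling schedule (Interventional substudy, Collection and storage of biospecimens) lists two separate early postoperative draws, "3–10 days after surgery, 1 month after surgery", followed by draws every 3–6 months for three years. It then sets one tolerance for all of them: "We will allow a maximum deviation of ±1 month around each scheduled postoperative draw to accommodate clinical logistics". A sensitivity analysis follows, "excluding samples collected outside the ±2-week window and re-estimating MRD dynamics and their correlation with outcomes".

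The 1-month draw carries the treatment decision. The abstract says "adjuvant therapy can be avoided for patients whose MRD is undetected at 1 month after surgery", and adds a major pathological response (MPR) as a further condition after neoadjuvant therapy. The Experimental arm section repeats the rule for treatment-naive patients: "patients whose MRD is undetected 1 month after surgery will enter surveillance". Their results "will be provided to clinicians and patients 6–8 weeks after surgery". For neoadjuvant-treated patients the results are to be analysed within 4–6 weeks of surgery, and only those with both MPR and a negative 1-month result go without adjuvant therapy.

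The same section lets the day-3 sample stand in when the 1-month draw does not go ahead as scheduled. That allowance appears only in the paragraph on treatment-naive patients.

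**The concern.** A tolerance of one month suits draws that are 3–6 months apart. Around a draw scheduled at one month, it is as wide as the interval from surgery to the draw. A sample from the first days after surgery, or from the end of the second month, then counts as the 1-month sample, and the guided arm acts on that sample.

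The treatment actually given in the guided arm is at stake. The treatment-naive rule already accepts an early sample as a substitute, so there the tolerance mainly obscures whether the planned draw or the fallback was used. The neoadjuvant rule has no such substitute. There the tolerance opens a route to omitting adjuvant therapy that the Experimental arm section does not otherwise give. The ±2-week sensitivity analysis does not close it, because it re-estimates associations afterwards and does not restrict which sample drives care.

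**Working it through.** No power or alpha figure is involved; the check is window arithmetic. The article does not give a month in days, so 30.4 days is assumed, with 28 and 31 as the range.

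**Inputs**
- Draws at days 3–10, at 1 month, then every 3–6 months; tolerance ±1 month; sensitivity window ±2 weeks (Collection and storage of biospecimens).
- Neoadjuvant results analysed by week 6 = day 42; upfront results released by week 8 = day 56 (Experimental arm).
- Guided arm 378 of 756 (Figure 2 caption; Settings); neoadjuvant stratum 147, both groups together (Table 3).

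**Step 1: window of the 1-month draw.** Lower end = month − month = day 0. Upper end = 2 × month.

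| Month length (days) | Compliant span | Past day 42 | Past day 56 |
|---|---|---|---|
| 28 | day 0 to 56 | 56 − 42 = 14 | 56 − 56 = 0 |
| 30.4 | day 0 to 60.8 | 60.8 − 42 = 18.8 | 60.8 − 56 = 4.8 |
| 31 | day 0 to 62 | 62 − 42 = 20 | 62 − 56 = 6 |

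The whole of days 3–10 lies inside this span for every month length.

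**Step 2: the same tolerance on the early draw.** 3 − 30.4 = day −27.4 and 10 + 30.4 = day 40.4. The window opens before surgery, so the tolerance cannot work as a rule for the early draws.

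**Step 3: the neoadjuvant case.** Take a guided-arm patient with MPR whose only postoperative sample is a negative one from day 8. Under the Experimental arm section alone there is no 1-month result, and adjuvant therapy follows. Under the tolerance, day 8 lies within day 0 to 61, so the same sample can be counted as a negative 1-month result and therapy omitted. The two sections give opposite answers for one patient.

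**Step 4: how many.** The neoadjuvant stratum is 147/756 = 19.4% of the substudy. If it splits between the groups as the whole does (an assumption), the guided part is 147 × 378/756 = 73.5 patients. Only those with MPR, a negative early sample and no true 1-month draw are exposed. The article gives none of these proportions, so no count can be derived.

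**Step 5: how long a missed positive would go untreated.** The next look is the first surveillance draw, 3–6 months on, or 6 + 1 = 7 months with the tolerance applied to that draw.

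**Step 6: the plan's own ±2 weeks on the decision draw.** 30.4 − 14 = day 16.4 to 30.4 + 14 = day 44.4 (days 14–42 for a 28-day month, 17–45 for a 31-day month). This excludes days 3–10. The upper end leaves 56 − 44.4 = 11.6 days to week 8 for upfront patients but lies 44.4 − 42 = 2.4 days past week 6 for neoadjuvant patients, so the window also needs a limit tied to the result time.

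**The case against.** The strongest reply is that the tolerance sentence is a loosely worded general allowance, not a decision rule. The schedule lists the early and 1-month draws separately, and the fallback sentence would be pointless if an early sample already counted as the 1-month one. A window that opens before surgery shows that the literal reading was not meant. This is a fair guide to intent. It does not settle what ten centres should do with a sentence that covers every postoperative draw, and it argues for correcting the wording.

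The late end is largely answered. A neoadjuvant patient without a negative 1-month result in time defaults to adjuvant therapy, because only MPR with a negative result avoids it. For upfront patients the overrun is 0–6 days, and the reporting times would in practice cap a usable sample. What stands is that they are not stated as limits on the draw, so the two sections conflict.

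The article is condensed, and the full protocol may hold visit windows that are not shown. The criticism is therefore confined to the tolerance that is stated, not to the absence of a separate window.

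A reader might infer more than the documents support:
- That the two-year DFS comparison is invalidated. The tolerance does not change patients' grouping; it can change the treatment received within the guided arm.
- That all 378 guided-arm patients are exposed. Upfront patients already have a stated early-sample fallback, so the new route to omission is confined mainly to neoadjuvant patients with MPR.
- That early samples are less accurate. The article gives no such comparison, and its introduction describes a landmark range from 3 days to 1 month.
- That patients lose adjuvant therapy for good. Surveillance continues and a later positive starts treatment, so the harm is delay.

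**Conclusion.** The point holds as a badly fixed stated rule. As written, the decision draw is compliant from day 0 to about day 61, overlaps the day 3–10 draw, and can fall after the result is due by about 19 days (14–20) in neoadjuvant patients and about 5 days (0–6) in upfront patients. These figures rest on reading the tolerance literally and on a month of 28–31 days.

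The consequence is narrow. It falls chiefly on guided-arm neoadjuvant patients with MPR, where one section requires a negative 1-month result and another lets an early sample pass as one. Their number is unknown. The change is worth making because the rule governs who forgoes adjuvant therapy, which is the intervention under test, and recruitment began in April 2025.

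**What to change.** In Collection and storage of biospecimens:
- Limit ±1 month to the 3–6-monthly surveillance draws and keep the early draw at days 3–10.
- Hold the 1-month decision draw to the plan's own ±2 weeks (about days 16–44), taken early enough for the result to be ready by week 6 (neoadjuvant) or week 8 (upfront).

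In the Experimental arm section:
- State that a day 3–10 sample never counts as the 1-month result in neoadjuvant patients. Without a valid negative 1-month result they receive adjuvant therapy, as that section already implies.
- For upfront patients, use the early sample only as the fallback, and record when it was used.

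The latest usable draw depends on assay turnaround, which the article does not give. For neoadjuvant patients it is day 42 minus the turnaround: day 35 if 7 days is assumed, day 28 if 14. A draw on the nominal date leaves 42 − 30.4 = 11.6 days, so with a longer turnaround the week-6 time itself needs review. The neoadjuvant limit should not be imposed on upfront patients, since it could displace a usable later sample with an early one.

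The cost is a small change of wording in two sections, less scheduling slack at one visit, and adjuvant therapy for a few MPR patients without an in-window sample, which runs against the de-escalation aim. No extra blood draws are needed, and draw dates are already required for the ±2-week analysis.

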#### MRD assay

In this study, we will use tumor-informed ctDNA detection, which is consistent with the methodology described in the *circulating tumor DNA assay* section.

### Interventions

#### Experimental arm (ctDNA-guided management)

In the ctDNA-guided arm, for treatment-naive patients, the results of ctDNA-MRD detected from blood before surgery, on Day 3 and 1 month after surgery will be provided to clinicians and patients 6–8 weeks after surgery. Notably, blood samples obtained on postoperative Day 3 may not be obtainable consistently in clinical practice. Thus, patients whose MRD is undetected 1 month after surgery will enter surveillance with blood sampling every 3–6 months during follow-up without additional adjuvant therapy. Blood samples obtained 3 days after surgery may serve as an alternative source of data in circumstances where blood sampling 1 month after surgery is not performed as planned. Furthermore, the concurrent availability of specimens from day 3 and 1 month after surgery facilitates a more robust assessment, wherein the Day 3 data provide supplementary context. Adjuvant therapy will be initiated if the patient’s MRD status is positive or if progression is suggested by imaging. The MDT will recommend specific treatment strategies on the basis of prior therapy, histology, and gene mutation. Treatment decisions will be individualized but guided by national guidelines to ensure consistency across centers.

For neoadjuvant-treated patients, ctDNA-MRD results of blood samples collected before/during neoadjuvant therapy, before surgery, and after surgery will be analyzed within 4–6 weeks after surgery. Patients will receive adjuvant therapy if any of the following criteria are met: the major pathological response is not reached (non-MPR) or postoperative ctDNA positivity conditions are met. Only patients who achieve MPR and negative ctDNA results 1 month after surgery will avoid adjuvant therapy, with surveillance of ctDNA-MRD detection performed every 3–6 months. Therapy will begin if ctDNA becomes positive.

If adjuvant therapy is indicated postoperatively after assessment, the MRD assessment will be performed after chemotherapy is completed (within weeks 3–4 in the final cycle of treatment).^[29]^ If MRD is positive, the patient will continue adjuvant therapy; otherwise, maintenance treatment will be stopped. Subsequent MRD monitoring should be performed every 3–6 months, with positive results or imaging progression triggering MDT discussion for treatment and negative results confirming therapy termination. If MRD persists after standard adjuvant cycles, the treatment duration will be extended.

#### Control arm (standard treatment)

In the control arm, patients will receive standard postoperative management and follow-up. For patients receiving regular MRD testing, their clinicians will be blinded to the initial ctDNA results, which can be disclosed upon request after 6 months.

#### Discontinuing or modifying the intervention

Below are predefined cases in which patients will be removed from the study intervention but will continue routine clinical care, such as clinic visits, labs, and imaging, per their clinicians:

(1) The patient cannot comply with protocol requirements.

(2) The patient develops a malignancy that requires treatment, which will interfere with this study.

(3) The patient is lost in follow-up.

### Outcomes

The primary endpoint of this clinical trial is the two-year DFS rate after surgery, defined as the interval from the surgical date to objectively confirmed disease recurrence or death from any cause.

Secondary outcomes of interest include (1) overall survival (OS), (2) total treatment cost 24 months after surgery, (3) incremental cost effectiveness ratio (ICER), (4) sensitivity of the novel recurrence prediction model developed in the observational substudy, (5) timely diagnosis of recurrence in the new follow-up model developed by the observational substudy, and (6) ctDNA characterization during neoadjuvant/adjuvant therapy and its associations with clinical outcomes, including short-term efficacy (radiological and pathological response) and long-term survival. Total treatment cost refers to the expense of lung cancer-related treatment for the patient during the research period, including the drug cost, follow-up treatment cost, drug management cost (consultation fee, antitumor drug allocation fee, intravenous infusion fee, nursing fee, *etc*.), cost of follow-up laboratory tests and imaging, and management cost of adverse reactions of grade 3 or greater, with an incidence rate of more than 5%.

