## Overview of the study design

This study includes two interlinked parts: an observational substudy and a prospective interventional substudy. Patients will be recruited from 10 tertiary clinical centers in China (Table 1), including stage IA-IIIA NSCLC patients who are initially treated or receiving neoadjuvant therapy. Each site has a high volume of eligible patients (> 1000 patients with early-stage NSCLC each year) and has expertise in enrolling patients and the ability to collect and store biospecimens. Patients will be followed after surgery, and blood collection will be performed at prespecified time points.

**Table 1 j_jtim-2026-0023_tab_001:** Medical centers of the REMODEL study

Peking University People’s Hospital
Guangdong Provincial People’s Hospital
Jiangsu Cancer Hospital
Shanghai Chest Hospital
The Second Xiangya Hospital, Central South University
Shenzhen Third People’s Hospital
Zhongshan Hospital, Fudan University
Peking University First Hospital
Wuhan Union Hospital
Shandong Cancer Hospital

The observational substudy aims to develop a novel multidimensional approach for noninvasive postoperative recurrence monitoring of NSCLC by innovatively integrating multiomics data, including clinicopathological features, plasma metabolomics, proteomics, cell-free DNA (cfDNA) features and radiomics, through artificial intelligence algorithms. Model development will leverage perioperative blood samples from early-stage NSCLC patients in a retrospective cohort, with external validation performed using samples of prospectively recruited patients.

The prospective interventional substudy will evaluate the feasibility, safety and clinical efficacy of ctDNA-MRD-based treatment intensification/de-escalation strategies in real-world settings while exploring the association between postoperative ctDNA-MRD monitoring dynamics and clinical outcomes. We will divide patients into standard treatment and ctDNA-MRD-guided groups, primarily comparing the two-year DFS rate and the total cost of treatment 24 months post-operative, as well as externally validating the sensitivity of the novel monitoring method established by the observational substudy.

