### Statistical analysis

Continuous variables will be described as the mean (with standard deviation [SD]) or median (with interquartile range [IQR]) depending on whether they fit a normal distribution. Categorical variables will be described as counts and percentages. Comparisons between groups will be performed using appropriate statistical tests (*chi-square* test for categorical variables; Student’s *t* test or Mann^‒^ Whitney *U* test for continuous variables). To address the potential confounding variable introduced by preference-based group allocation, we will implement propensity score methods, including propensity score matching (PSM) and inverse probability of treatment weighting (IPTW).^[30]^ Multivariate analyses for covariate correction will be conducted using logistic regression, linear regression, and Cox proportional hazards regression, depending on the type of outcome variables. Variance inflation factors (VIFs) will be assessed *via* correlation matrices, with variables with a VIF < 3.0 retained. Firth’s penalized maximum likelihood bias reduction method for Cox regression will be implemented to handle the monotone likelihood. All analyses will be performed using R (version later than 4.4.0), and a two-tailed p value of < 0.05 will be considered to indicate statistical significance. Detailed methodologies for outcome analysis, subgroup evaluation, and sample size estimation are provided in Supplementary materials 3–4.

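### The cost definition counts severe adverse reactions only above an undefined 5% incidence, which can distort the between-arm cost difference and the ICER in either direction

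*Protocol article*

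**What the plan says.** The Outcomes section of the protocol article lists the cost endpoints as secondary: "2) total treatment cost 24 months after surgery, (3) incremental cost effectiveness ratio (ICER". It then defines the first of them: "Total treatment cost refers to the expense of lung cancer-related treatment for the patient during the research period". The components that follow are drugs, follow-up treatment, drug administration, "cost of follow-up laboratory tests and imaging", and lastly "management cost of adverse reactions of grade 3 or greater, with an incidence rate of more than 5" percent.

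The text does not give the denominator of that incidence. The ctDNA assay and the tumor-informed panel are neither named nor excluded.

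Four other places bear on the point:
- **Interventions, experimental arm:** guided patients with undetected MRD at one month go without adjuvant therapy (after neoadjuvant treatment, only if they also reach a major pathological response). Treatment stops in those who become negative.
- **Interventions, control arm:** some controls are also MRD-tested, with clinicians blinded to the initial results.
- **Data collection (interventional substudy):** treatment details and treatment-related adverse events go into a central database.
- **Discussion:** if prognosis does not differ, a clear reduction in adverse effects or in costs could still support using MRD in practice.

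**The concern.** An incidence threshold is not neutral when the strategies under comparison change how many patients are exposed. The same reaction, equally likely in any treated patient, can pass 5% in one arm and fail it in the other. If the rule is applied by arm, its cost is charged to one arm only. If it is applied to the pooled sample, the cost may vanish from both arms although more of it arose in one. Either way the numerator of the ICER changes for a reason unrelated to what was spent.

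A related gap lies in the same definition. The assay is a cost of the guided strategy itself, yet the reader cannot tell which tests count, or in which arm. Cost is a secondary endpoint, but under the Discussion's second scenario a cost reduction is one of two results that could carry the recommendation.

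**Working it through.** **No plan figure to reproduce.** The article gives no cost effect, unit price or reaction rate. The sample sizes used below are consistent: 609 + 147 = 756 = 378 + 378, and 756 + 160 = 916.

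**What the threshold means in patients.** 5% of 378 is 18.9, and 5% of 756 is 37.8. Under a per-arm rule, a severe reaction seen in up to 18 patients of an arm adds no cost there. Under a pooled rule, one seen in up to 37 patients overall adds no cost at all.

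**Main illustration.** Assumptions, none of them in the document: a grade 3 or greater reaction occurs in 8% of treated patients, and 70% of controls and 30% of guided patients are treated. Arms are equal, as planned.
- Control incidence: 0.08 × 0.70 = 5.6%.
- Guided incidence: 0.08 × 0.30 = 2.4%.
- Pooled incidence: (5.6 + 2.4)/2 = 4.0%.
- True difference, control minus guided: 5.6 − 2.4 = 3.2 points.

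With a management cost of *c* per reaction, the true saving per patient from this reaction is 0.032*c*. The recorded saving depends on the reading:

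| Reading of the 5% rule | Control counted | Guided counted | Recorded saving |
|---|---|---|---|
| Per arm | 5.6% | 0 (2.4% fails) | 0.056*c* |
| Pooled | 0 (4.0% fails) | 0 | 0 |
| Among treated | 5.6% (8% passes) | 2.4% (8% passes) | 0.032*c* |

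The per-arm reading overstates the saving by a factor of 0.056/0.032 = 1.75. The pooled reading removes it. The among-treated reading is right for this reaction, but it still drops any reaction with a rate *r* of 5% or less among treated patients. The lost difference is *r* × (0.70 − 0.30) = 0.4*r*, up to 2.0 points for each such reaction.

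**Other assumed incidences, control against guided:**
- 6% and 4%: true difference 2 points; per arm 6; pooled 0, because the pooled rate is exactly 5% and does not exceed the threshold.
- 8% and 3%: true difference 5; per arm 8; pooled 5, because the pooled rate is 5.5%.
- 4% and 4%: true difference 0, and no distortion under either rule.

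**Assays.** The interventional substudy's biospecimen section schedules three perioperative draws (before surgery, at 3–10 days, at one month) and then one every 3–6 months. To month 24 that is 3 + 24/6 = 7 to 3 + 24/3 = 11 draws. The 4 to 8 surveillance draws could be read as follow-up laboratory tests. The preoperative draw and the panel built from tumor tissue do not fit that item naturally. No price is given, so the effect of leaving them out cannot be sized.

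**The case against.** The best defense is that the distortion is conjectural. All the rates are assumed, one reading (among treated) gives the correct answer in the main example, and with equal incidences nothing goes wrong. A cut-off also spares the costing of rare events that barely move a mean. Nor is lower exposure in the guided arm guaranteed in size, since MRD-positive patients outside the usual indications may be treated there. All of this limits how far the size and direction can be predicted. It does not rescue the rule, which gives different answers from the same data according to a choice that the text leaves open.

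A reader might infer several stronger things that the document does not support:
- **That the bias favors the guided arm.** In the main example a pooled filter hides a real saving and works against that arm.
- **That the ctDNA assay is left out.** The component list is introduced as inclusive, and surveillance assays may be covered by its laboratory-test item. This is ambiguity, not omission.
- **That skewed costs will be compared by a rank test, so that the ICER is biased.** In the Statistical analysis section the clause "depending on whether they fit a normal distribution" governs how variables are described. The "Mann^‒^ Whitney *U* test for continuous variables" is a generic option that does not mention cost. The same section says "Multivariate analyses for covariate correction will be conducted using logistic regression, linear regression, and Cox proportional hazards regression", adds propensity methods, and sends outcome methods to supplements that are not shown. A rank test does not test a mean difference, but a choice of test cannot bias an ICER, which is built from mean differences.
- **That cost is a co-primary endpoint.** The design overview does speak of "primarily comparing the two-year DFS rate and the total cost of treatment 24 months post-operative", but the interventional Settings, the Figure 2 caption and the Outcomes section all make two-year DFS primary, and Outcomes lists cost as secondary.

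**Conclusion.** The concern holds for the incidence filter. As written, the rule can distort the between-arm cost difference and the ICER, and the direction depends on a denominator that is not stated. Under the assumed 5.6% and 2.4%, a true gap of 3.2 points is recorded as 5.6 or 0. These figures show the mechanism and do not forecast its size, because reaction rates, the proportions treated and unit costs are not in the document. The conclusion rests on adjuvant exposure differing between arms, which the guided strategy intends. On the assay, what stands is that its place in the cost definition needs stating. That the comparison is certain to be biased, or biased toward the guided arm, is not shown.

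**What to change.** In the Outcomes definition, delete the 5% incidence condition. Count the management cost of every grade 3 or greater treatment-related reaction, patient by patient, in both arms. The adverse events are already to be recorded, so no new event collection is needed.

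In the same definition, state that the tumor-informed panel and all ctDNA assays used for management, including the perioperative ones, are counted in the guided arm, and that blinded research assays in controls are not.

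As a minor wording correction, align the design overview with the secondary status of cost.

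The price is slightly more costing work for the less frequent reactions and for the assays. The cost difference may move in either direction. Recruitment began in April 2025, so the wording should be settled before outcomes are compared between arms.
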